## The Social Norm intervention

In line with the ToC the Balika Bodhu intervention will be developed heavily drawing on CARE's IMAGINE model (CARE, 2019), and on SAFE, a project spearheaded by icddr,b and aimed at promoting SRHR and addressing violence against women in slums of Dhaka ([name] et al., 2018).

Balika Bodhu intervention will be implemented by Nari Maitree, an NGO working on women's issues. The research team will conduct both quantitative and qualitative monitoring for documenting implementation fidelity. This will allow tracking of any deviations from the charted programme, which will be important to take into consideration during interpretation of the results. Effectiveness of the intervention will be assessed in changing social norms endorsing denial of SRHR to MAGs and in empowering them to demand, access and practice SRHR. The intervention will involve a 12-month gender transformative participatory programming for: (1) empowering MAGs and (2) creating an enabling environment in the family and the community for the MAGs to demand, access and practice SRHR. For empowering MAGs their intrinsic, instrumental and collective agency will be promoted. Special attention will be paid to incorporate two critical elements, often missing from many empowerment programmes – development of critical consciousness and movement building. The intervention will particularly focus on promoting rights of the MAGs through enhancement and exercise of the notions of choice and consent.

The intervention will target Married adolescent girls, their spouses, and elderly/influential community members. Thirty-six 2-hour weekly sessions will be conducted with MAGs. The session topics will be categorized into two broad headings: i) Health and life skills sessions covering, for example topics such as sex and gender, rights, marriages, SRHR (e.g., first conception, birth spacing, contraception, healthy relationships, polygamy, divorce, gender-based violence (GBV), communication and negotiation, anger and conflict management, goal setting, household budgeting, activism, leadership skills, and community action planning, and ii) Business and entrepreneurship sessions, which will basically include sessions smart planning of businesses (e.g., market research, business planning, and adding value).

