## Monitoring of Balika Bodhu

We propose routine quantitative monitoring and reporting of number of group sessions by schedule, duration of group session, number of session attendants, number of activities performed, etc. We will also keep record of how many sessions and which particular sessions the participants are attending. This will allow us to measure the impact of number of session attendance on the primary and secondary outcomes. It is preferable to conduct such reporting bi-weekly so that problems can be identified and fixed before it is too late. Presentation of performance of each cluster graphically will allow all staff to understand their own performance in relation to others' and may encourage catching up.

Monitoring qualitative aspects of the intervention is of utmost importance. We will conduct three rounds of qualitative monitoring as follows:

| Round   | Timing                | Data collection techniques and numbers                                   |
|---------|-----------------------|--------------------------------------------------------------------------|
| Round 1 | 3 rd month | • Session observation : 5 sessions with MAGs, and 3 with husbands |

|         |                       |                                                                                                                                                                                                                                                                                                                                                                                                                                           |
|---------|-----------------------|-------------------------------------------------------------------------------------------------------------------------------------------------------------------------------------------------------------------------------------------------------------------------------------------------------------------------------------------------------------------------------------------------------------------------------------------|

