### **Sample Size Calculation and Outcome (Primary and Secondary) Variable(s)**

Clearly mention your assumptions. List the power and precision desired. Describe the optimal conditions to attain the sample size. Justify the sample size that is deemed sufficient to achieve the specific aims.

The sample size for the survey of MAGs was calculated based on the primary outcomes "ability of a MAG to achieve own choice regarding: (1) FP use; (2) conception; and (3) SRH service uptake". Considering a cluster size of 22 married adolescent girls and their husband, and assuming a 50% prevalence rate of ability of a MAG to achieve own choice in SRH issues among this group (as unknown), 15% effect size, an Intra-Cluster Correlation of 0.05, 5% significance level and 80% power we required 16 clusters per arm making the total number of clusters 32. Considering a 10% non-response rate at baseline, 20% refusal rate among MAGs interviewed at baseline to participate in the intervention, and another 15% drop out rate at endline among the MAGs participated in the intervention, the group size increased to 35 and total sample size increased to 1,120 MAGs. As these considerations provided us with the maximum sample size, this current sample size will allow us to measure the changes in all other secondary outcomes of the study.

The husband of the selected MAGs will also be included in the study to measure the secondary outcomes related to their knowledge and attitudes regarding SRHR relevant to them and the MAGs.

To assess social norm change we focused on social norms around the MAGs' consent and choice in SRH. We will assess this change surveying adult community members aged 35-59 years. Since the prevalence of positive social norms around consent and choice in SRH issues is unknown among this population we assumed it as 50%. Considering a 15% effect size, 5% significance level, 80% power and 5% non-response rate, we required 540 community members (270 females and 270 males) from 32 clusters. Dividing the numbers by number of clusters and then rounding up the total sample size increased to 576 (nine females and nine males from each cluster).

The qualitative sample size includes 6 KIIs, 32 IDIs and 8 FGDs at baseline and endline.

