Intention-to-treat (ITT) analysis will be used during assessing the impact of the intervention. Thus, all the MAGs enrolled at baseline and could be successfully interviewed at endline will be included in the analysis irrespective of their actual level of participation in the intervention activities. The information on participation of study participants in the intervention activities will come from the programme monitoring data and will also be used in the models. The impact of the intervention on primary and secondary outcomes will be assessed using risk ratios/regression coefficients derived from binary/linear regression analyses for measuring change in outcomes in the intervention arms relative to change in the control arm. Significance level will be set at  $p < .05$  for all analyses. The data will be analysed using STATA 16.

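### The protocol commits to ITT but says participation data will be used in the models, without separating an attendance analysis from the randomised comparison

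*Protocol*

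**What the plan says.** Under Quantitative data analyses, the protocol says "Intention-to-treat (ITT) analysis will be used during assessing the impact of the intervention". Girls enrolled at baseline and interviewed at endline "will be included in the analysis irrespective of their actual level of participation in the intervention activities". The next sentence says that records "on participation of study participants in the intervention activities will come from the programme monitoring data and will also be used in the models". After that, one sentence describes the impact models: binary or linear regressions giving risk ratios or coefficients "for measuring change in outcomes in the intervention arms relative to change in the control arm". The section names no other model for the effect of the intervention.

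The purpose of the attendance records is given under Monitoring of Balika Bodhu, where the number of sessions attended, and which ones, is to be recorded: "This will allow us to measure the impact of number of session attendance on the primary and secondary outcomes".

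Three further facts matter. The Study design section makes the second arm an untreated control. The Social Norm intervention section states "Thirty-six 2-hour weekly sessions will be conducted with MAGs", so a girl's attendance can run from 0 to 36. The sample size section expects a "20% refusal rate among MAGs interviewed at baseline to participate in the intervention", and Household enumeration, sampling and recruitment says that everyone interviewed at baseline will be sought again at endline. Girls who refuse the programme therefore stay in the analysis with zero sessions.

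**The concern.** Attendance is a consequence of assignment. It is fixed at zero for every control girl and varies only among intervention girls, who choose (or are allowed) how often to come. An ITT comparison holds because nothing observed after randomisation enters it. A participation variable placed beside arm breaks that. The arm coefficient then answers a different question, namely how girls in intervention villages with a fitted attendance of zero differ from all control girls.

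The sentence on participation sits between the ITT commitment and the only impact models described, so an analyst could reasonably carry it into those models. What is at stake is which coefficient becomes the trial's primary result. An effective programme could appear to do nothing or to do harm, and an ineffective one could show a spurious arm effect.

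The monitoring section raises a related problem even if the attendance analysis is kept apart. The primary outcome is a girl's own decision-making agency, which plausibly affects whether she can attend. A regression on sessions attended then mixes cause and consequence, and calling its result an impact is not justified.

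**Working it through.** **1. The plan's own figure.** The protocol disputes no number on this point, but its design was reproduced to set the scale. Inputs from the sample size section: 50% versus 65% (the 15% effect size read as percentage points), 5% significance (taken as two-sided), 80% power, ICC 0.05, and "Considering a cluster size of 22 married adolescent girls and their husband".

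- Two-proportion formula without continuity correction: 170 per arm.
- Design effect: 1 + (22 - 1) × 0.05 = 2.05, and 170 × 2.05 = 348.5.
- 348.5 / 22 = 15.84, rounded up to 16 clusters per arm. This matches the protocol.
- Inflation: 22 / (0.90 × 0.80 × 0.85) = 35.9 against the stated 35, which is close enough here; 35 × 32 = 1,120.

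The planned effect in SD units is 0.15 / √(0.5 × 0.5) = 0.30.

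**2. What the arm coefficient becomes.** Let A be arm, S sessions attended, and Y = α + βA + γS + error, with S = 0 whenever A = 0. Least squares takes γ from the intervention arm alone, and

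β = (mean Y, intervention - mean Y, control) - γ × (mean S, intervention).

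The bracket is the ITT estimate. So β equals it only when γ × mean S is zero.

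**3. Numbers.** These inputs are assumptions, not protocol figures: 80% accept the programme and attend about 24 of 36 sessions, sessions = 24 + 6L + noise of SD 4 where L is a standard-normal prognostic factor, and the effect of L on the outcome is 0 or 0.3 SD. Ignoring the cap at 36:

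- Mean S = 0.8 × 24 = 19.2.
- Variance of S = 0.8 × (36 + 16) + 0.8 × 0.2 × 24² = 41.6 + 92.16 = 133.76.
- If benefit is proportional to sessions, γ = 0.30 / 19.2 = 0.0156 and the shift in β is 0.30.
- If attenders have better prognosis, the extra slope is 0.3 × (0.8 × 6) / 133.76 = 0.0108, a further shift of 0.0108 × 19.2 = 0.21.

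The formula therefore predicts β of 0.00, -0.21, 0.30, 0.09 and -0.21 for the five rows below.

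**4. Simulation.** 16 villages per arm, 27 girls analysed per village (35 × 0.90 × 0.85 = 26.8, keeping refusers, with the 15% loss applied to all), ICC 0.05, linear outcome, cluster-robust errors, 400 runs per row. Cells show the mean arm coefficient in SD and the share of runs with p < 0.05.

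| Assumed scenario | Arm only | Arm plus sessions |
|---|---|---|
| True 0.30, proportional to sessions, no confounding | 0.29; 79% | -0.01; 6.5% |
| True 0.30, proportional, attenders better prognosis | 0.30; 83% | -0.20; 35% |
| True 0.30, unrelated to sessions, no confounding | 0.29; 82% | 0.30; 65% |
| True 0.30, unrelated, attenders better prognosis | 0.30; 86% | 0.10; 12.5% |
| True 0, attenders better prognosis | 0.00; 7.5% | -0.20; 36.5% |

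Simulation and formula agree. In the last row the Monte Carlo standard errors are 1.3 and 2.4 percentage points. The direction of confounding is also an assumption: if attenders had the worse prognosis, the formula turns the 0.21 shift upward.

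**The case against.** The strongest reply is that the protocol never says attendance enters the ITT model beside arm. It says only that the data will also be used in the models, without saying which models or how. The monitoring section gives attendance a question of its own, the effect of the number of sessions, and the Social Norm intervention section says that departures from the planned programme will be considered when results are interpreted. An additional exposure-response analysis is a fair reading, and exact model specification is often left to a statistical analysis plan, which is not shown here. This stands: a reader might infer that ITT has been abandoned, and the text does not support that.

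A reader might also infer that the treatment effect would vanish. That happens only when all benefit runs through the girl's own sessions. The protocol also plans husband, couple and community-member sessions and community-level activities, which can reach a girl who seldom attends. In one simulated scenario the coefficient stayed unbiased and only lost precision. The documents also contain no data on who attends, so the confounding is plausible but not shown.

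The reply does not remove the point. The participation sentence is an affirmative statement placed among the impact models, not a detail left open. On the benign reading, the monitoring section still calls a self-selected association an impact.

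**Conclusion.** The point holds in conditional form. The protocol commits to ITT, says participation data will be used in the models, describes only arm-comparison models, and nowhere separates an attendance analysis from them. If attendance is entered beside arm, the coefficient stops estimating the ITT effect. It can be removed, reversed, attenuated or merely less precise: -0.20 to 0.30 SD over the simulated scenarios for a true 0.30 SD. With no true effect and better-prognosis attenders, the arm coefficient was significant in about 37% of runs, against 7.5% with arm alone.

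That the coefficient changes its meaning follows from attendance being post-randomisation and structurally zero in one arm. The sizes rest on assumed attendance, dose effect and confounding, and should be read as illustration. If attendance is analysed separately, what remains wrong is the claim to measure an impact.

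**What to change.** 1. In Quantitative data analyses, replace the participation sentence. State that the impact (ITT) models, for husbands' outcomes as well as the girls', contain arm, the baseline outcome and pre-randomisation covariates only, with no participation data. Because the baseline survey follows village randomisation, add that any covariates taken from it must be recorded before the first session.
2. Add that attendance is examined in a separate supplementary analysis, labelled non-randomised and exploratory.
3. In Monitoring of Balika Bodhu, change the stated aim from measuring an impact of attendance to describing its association with the outcomes.

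A complier analysis, with assignment as the instrument for sessions attended and clustering by village, is optional. If used, it must say that its exclusion restriction is doubtful, because husbands and community members in intervention villages also receive sessions.

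The cost is a few sentences. The 16 clusters per arm and 1,120 girls stay as they are, and no new data are needed. The change should be made before endline data are analysed.

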Spouses of the MAGs will receive 20 2-hour bi-weekly sessions. The session topics will cover: sex and gender, rights, marriages, registration, dowry, conception and contraception, healthy relationships, polygamy, divorce, gender-based violence (GBV), communication and negotiation, anger and conflict management, goal setting, and household budgeting.

A total of three 2-hour couples sessions will be held, each to be delivered every two months, starting from the 6th month of the intervention. The session topics will include teenage pregnancy, unwanted pregnancy, and action planning. Elderly and influential community members will have three 2-hour bi-monthly sessions starting from the 6th month of the intervention, covering topics related to teenage pregnancy, unwanted pregnancy, and action planning.

MAGs with leadership qualities will be identified and trained to conduct campaigns and activism. They will be put in contact with other girls' groups and networks, mentored and given access to resources to execute at least two community-level social norm activities. These leaders will also receive training on income generating.

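### The intention-to-treat paragraph puts programme participation into the models without separating it from the impact regressions; as a covariate in an endline or change model it would stop the arm coefficient being the intention-to-treat effect

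*Protocol*

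**What the plan says.** The impact analysis is one paragraph under Quantitative data analyses in the Protocol. It makes three statements in sequence.

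1. The analysis is by intention to treat. Girls enrolled at baseline and interviewed at endline "will be included in the analysis irrespective of their actual level of participation in the intervention activities".
2. Information on participation "in the intervention activities will come from the programme monitoring data and will also be used in the models".
3. Impact is assessed from "risk ratios/regression coefficients derived from binary/linear regression analyses for measuring change in outcomes in the intervention arms relative to change in the control arm".

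The paragraph names no separate dose-response, per-protocol or secondary model. It does not say whether participation is a covariate, an interaction term or the exposure in another model.

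Two other places bear on the point. Monitoring of Balika Bodhu gives a purpose for the attendance records: "This will allow us to measure the impact of number of session attendance on the primary and secondary outcomes". The Social Norm intervention describes components that do not need the girl to attend, such as husbands' sessions, and also: "Elderly and influential community members will have three 2-hour bi-monthly sessions". Under Study design the second arm receives no programme at all.

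**The concern.** Participation is decided after allocation, is observed only in the intervention arm, and is one of the routes by which the programme is meant to work. If it stands beside arm in the regression that yields the impact estimate, the arm coefficient is the contrast between intervention girls with no participation and all controls. That is not the effect of being assigned to the programme. It is not a clean effect in non-attenders either, because non-attenders select themselves while the controls they are compared with are unselected.

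The primary estimate is at stake. An analyst could reasonably fit the regression with or without participation and point to the same paragraph in support. The two can give very different answers.

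**Working it through.** **Inputs from the Protocol (Sample Size Calculation)**
- "Considering a cluster size of 22 married adolescent girls and their husband"; 16 clusters per arm, intra-cluster correlation 0.05, 5% significance, 80% power.
- "assuming a 50% prevalence rate of ability of a MAG to achieve own choice in SRH issues", with a 15% effect, read as absolute (50% against 65%).
- "20% refusal rate among MAGs interviewed at baseline to participate in the intervention".

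**Assumptions not in the Protocol**
- 20% of intervention girls attend nothing. The rest either attend a graded share (Beta(4,2), mean 4/6 = 0.667) or attend everything.
- The share of the effect that passes through the girl's own attendance is varied.
- The outcome is binary, as in the sample-size section. The primary outcome is defined elsewhere as a summed score; the algebra in step 2 holds for either.

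**Step 1. Reproduce the plan's figure.**
n per arm = [1.96·√(2·0.575·0.425) + 0.8416·√(0.25 + 0.2275)]² / 0.15² = 169.3, so 170.
Design effect = 1 + 21·0.05 = 2.05.
170·2.05 = 348.5 girls; 348.5/22 = 15.84, so 16 clusters per arm. The stated figure reproduces, and power at 16 × 22 is 80.6%.

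**Step 2. Algebra with participation as a covariate.**
Write E[Y] = b0 + b1·arm + b2·P, with P = 0 in all controls. Then

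intention-to-treat effect = b1 + b2·mean(P), so b1 = intention-to-treat effect − b2·mean(P).

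With graded attendance, mean(P) = 0.8·0.667 = 0.533.
- All 15 points through attendance: b2 = 0.15/0.533 = 0.281 and b1 = 0.
- Half: b2 = 0.075/0.533 = 0.141 and b1 = 0.075.
- None: b2 = 0 and b1 = 0.15.

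**Step 3. Precision.** Even when b1 keeps its value, its variance rises because arm and P are collinear. In the intervention arm the within-cluster part is multiplied by 1 + mean(P)²/Var(P). For all-or-none attendance this is 1 + 0.64/0.16 = 5.

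**Step 4. Simulation.** 400 trials per row, 16 + 16 clusters of 22, true total effect 0.15, endline linear model with cluster-robust errors. Power is the share of trials significantly positive. Ranges cover graded and all-or-none attendance.

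| Points of the 15 not depending on her attendance | Arm only: estimate, power | Arm + participation: estimate | Power |
|---|---|---|---|
| 0 | 0.15, 79–80% | 0.003–0.005 | 3–4% |
| 5 | 0.15–0.16, 78–80% | 0.05–0.06 | 9–12% |
| 7.5 | 0.15, 77–82% | 0.07–0.08 | 18–19% |
| 10 | 0.15, 77–79% | 0.09–0.10 | 25–28% |
| 15 | 0.15, 73–77% | 0.14–0.15 | 51–54% |

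Further runs that also covered change-score and time-varying models gave the same picture: arm-only power 76–83%, falling to 12–20% with half the effect through attendance and 47–55% with none. Across all runs without selection, adjusted power lies between 2% and 55%.

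If low attenders also have poorer prognosis (assumed 5 points per standard deviation), the adjusted arm coefficient becomes about −0.07 to −0.08 when all the effect runs through attendance, and about 0.07 when none does.

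**Step 5. Difference-in-differences.** The wording of the impact sentence also fits a model with arm, time and arm × time in girls seen at both rounds.
- If participation is fixed in time (the same value at both rounds), the arm × time term, centred within each girl, is orthogonal to every time-fixed variable. The linear estimate cannot change. Simulation agrees: 0.145 with and without participation. A risk-ratio version was also unchanged (log risk ratio 0.26 both ways; 77% and 76% significant).
- If participation is zero at baseline and positive at endline, the model is equivalent to the change-score model with P as a covariate, and the loss in step 4 returns.

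**The case against.** The strongest reply is that the faulty model is not written down. The paragraph does not call participation a covariate beside arm, and the monitoring section gives attendance a dose-response purpose. Saying that it is also used can be read as that extra analysis. The sentence on impact describes arm contrasts without mentioning participation, and its reference to change fits a difference-in-differences model, in which a time-fixed covariate does no harm.

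Much of this stands. A reader might infer that the protocol commits the primary model to adjustment for participation; the text does not go that far. A reader might also infer that a working programme would read as no effect. That is the limiting case in which everything passes through the girl's own attendance, and the sessions for husbands and community members make it unlikely to hold exactly. The attendance distribution and the strength of selection are assumptions.

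The reply does not remove the point. The clause sits between the intention-to-treat statement and the only impact regressions described, and nothing keeps the two uses apart. The harmless specification is one of several that the wording allows. This is a statement the protocol makes, so it is not simply detail left for a statistical analysis plan.

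**Conclusion.** The concern holds in conditional form. The protocol promises intention to treat and then brings a post-randomisation variable, zero throughout the control arm, into unspecified models.

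If participation is a covariate in an endline or change model, or time-varying in a difference-in-differences model, the arm coefficient is not the intention-to-treat effect. A true 15-point effect would then be estimated at about 0, about 8 points or about 15 points according to whether all, half or none of it runs through the girl's own attendance. Power would be between 2% and 55% instead of about 80%. If participation is time-fixed in a balanced linear difference-in-differences model, nothing is lost.

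The sizes rest on the assumed attendance, on the mediated share, and on a binary outcome with the protocol's sample-size inputs. The algebra in step 2 does not depend on those choices. The documents do not support the claim that the primary estimate is certainly lost. They do support the claim that the paragraph permits an analysis contradicting its own intention-to-treat statement.

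**What to change.** In the intention-to-treat paragraph, delete the clause that sends participation into the models. State that the intention-to-treat impact models for primary and secondary outcomes contain arm (and time, where change is modelled) and baseline covariates only.

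Move participation to a separately labelled secondary analysis. This can be the dose-response analysis that the monitoring section foresees, described as non-randomised, or a complier-average effect with randomised arm as the instrument. If the latter is used, note that sessions for husbands and community members can affect outcomes without the girl's attendance, which strains the exclusion restriction.

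The cost is a sentence or two in the analysis section. No data, sample size or budget changes.

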### **Quantitative data analyses**

Items in the survey questionnaires will be recoded so that all are anchored at 0. For example, for gender norms and attitudes, each item with scores ranging between 1 and 4 in the questionnaire will be recoded to 0–3. Negatively valenced items will be reverse-coded, so higher score indicates positive outcome. All the measurement scales used in the study will be validated using factor analysis. This exercise will allow us as well to reduce the number of items in the scales. Internal consistency (or reliability) of a scale will be measured using Cronbach's alpha. A scale with alpha equal to 0.60 or more will be considered acceptable. Scale validity will be measured using the Kaiser-Meyer-Olkin (KMO) test, where KMO equal to 0.60 or more will be considered acceptable. Once the final scale is constructed, a summative score will be obtained for each scale, and the scores will then be divided into tertiles.

During baseline we will explore the current situation in empowerment and SRHR among MAGs and their correlates, while at end line we will measure the impact of the social norms intervention on empowerment, on social norm change and promotion of demand, access and positive practices in relation to SRHR among the MAGs. Using the baseline survey data, the basic background characteristics (e.g., age, education,

religion, ethnic group) of the girl and community samples will be compared by arm (control, treatment) to check the arm balance. Descriptive analyses will be performed to report frequencies and percentages of different outcomes of interest. Chi-square, ANOVA and t-tests will be performed to check whether the study arms are covariate balanced. Linear and logistic regression analyses will be performed to identify the underlying factors for current situation in SRHR among MAGs.

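### The impact analysis names only binary/linear regression and makes no allowance for the 32 randomised villages, although the sample size assumes an intra-cluster correlation of 0.05

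*Protocol*

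**What the plan says.** Under *Cluster formation and randomization*, villages are the units of allocation: 32 are drawn and assigned 1:1. The sample size section plans accordingly. It starts from 22 girls per village ("Considering a cluster size of 22 married adolescent girls and their husband"), and then states: "an Intra-Cluster Correlation of 0.05, 5% significance level and 80% power we required 16 clusters per arm making the total number of clusters 32".

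Under *Quantitative data analyses*, impact on primary and secondary outcomes is to be assessed with "risk ratios/regression coefficients derived from binary/linear regression analyses for measuring change in outcomes in the intervention arms relative to change in the control arm". The same paragraph fixes the analysis set (everyone enrolled at baseline and interviewed at endline, whatever their participation), the 5% significance level and the software, Stata 16. Neither this section nor any other mentions a village random effect, GEE, cluster-robust standard errors or an analysis of village summaries.

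The girls and their husbands are a cohort interviewed at both waves. The community survey draws a fresh cross-section of 18 people per village at each wave.

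**The concern.** When villages are randomised, girls from one village carry partly the same information, and the standard error of the arm contrast must reflect that. The protocol allows for this when it sets the number of villages, then describes an analysis that, read as written, treats each girl as independently randomised. If the analysis is run that way, standard errors are too small, confidence intervals too narrow, and a result at p < .05 is weaker evidence than it appears. This concerns the primary test as well as the secondary ones.

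A smaller issue is the use of baseline. Comparing change with change subtracts the whole baseline value. Using the same value as a covariate lets the data decide how much of it to remove, and this is generally more precise.

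**Working it through.** **Inputs from the protocol.** Control proportion 50% and a 15% effect, read as 50% against 65%; alpha 5% (taken as two-sided, since sidedness is not stated); power 80%; ICC 0.05; 22 girls per village; 16 villages per arm; 35 selected per village; 10% baseline non-response; 15% endline drop-out.

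**The plan's own figure.**
- Two proportions, pooled variance, no continuity correction: 170 per arm.
- Design effect = 1 + (m − 1) × ICC = 1 + 21 × 0.05 = 2.05.
- Villages per arm = 170 × 2.05 / 22 = 15.84, rounded up to 16. The stated figure reproduces.
- Without the design effect: 170 / 22 = 7.7, so 8 villages per arm. About half of the villages are there because of clustering.

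**Girls analysed per village.** The sample size uses 22. The stated analysis set also keeps girls who decline the intervention, which gives 35 × 0.90 × 0.85 = 26.8 if the 15% loss applies to everyone.

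**Type I error if village is ignored.** Rate = 2 × [1 − Φ(1.96 / √DE)].

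| ICC of analysed outcome | Girls per village | Design effect | Type I error |
|---|---|---|---|
| 0.05 | 22 | 2.05 | 17.1% |
| 0.05 | 26.8 | 2.29 | 19.5% |
| 0.03 | 26.8 | 1.77 | 14.1% |
| 0.02 | 22 | 1.42 | 10.0% |
| 0.01 | 22 | 1.21 | 7.5% |

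At a design effect of 2.05 the true standard error is √2.05 = 1.43 times the naive one, so the naive one is about 30% too small. A beta-binomial simulation with 16 villages per arm and 20,000 runs gave 17.7% (22 per village) and 20.3% (27 per village).

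**If individual change is analysed.** The relevant quantity is the ICC of change: 0.05(1 − c) / [0.05(1 − c) + 0.95(1 − i)], where c and i are the correlations between waves of the village and individual components. The protocol gives neither. Taking c from 0 to 0.9 and i from 0.2 to 0.7 as assumptions:
- Regression on individual change, ignoring village: about 7% to 37%. At c = i = 0.5 the ICC of change is 0.05, and 17% to 20% returns.
- Regression pooling both waves, ignoring village and person: below 1% to about 18%.

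**Community survey.** With 18 per village, and 0.05 taken as an assumption because no ICC is stated for it, the design effect is 1.85 and the rate 15.0%.

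**What a valid analysis costs in power.** A t-test on village proportions (30 degrees of freedom) held its simulated type I error at 4.8% to 5.3%. Simulated power for 50% against 65% was about 78% with 22 girls per village and about 82% with 27.

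**Change against baseline as covariate.** With equal variances at both waves and baseline–endline correlation r, the variance factors are 2(1 − r) for change and 1 − r² for adjustment. The difference is 2(1 − r) − (1 − r²) = (1 − r)², which is never negative. The protocol does not give r. As an illustration, r = 0.2 gives 1.60 against 0.96, and r = 0.5 gives 1.00 against 0.75.

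**The case against.** The best defence is that the text is silent rather than wrong. It names a model family and an effect measure, and a linear or binary regression with village-clustered errors would still fit the wording. The authors plainly know that the design is clustered. Only the protocol is at hand, and a statistical analysis plan commonly supplies the variance estimator and degrees of freedom. It is therefore fair to say that an unadjusted analysis is inferred, not declared. But the paragraph does not defer to another document: it sets analysis set, effect measures, model, contrast, significance level and software, and omits the one feature on which the sample size depends. A plan that followed it literally would be invalid.

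Several stronger readings are tempting and do not hold.

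- A reader might infer that baseline is not used. It is: change is compared with change, so baseline enters by differencing. Adjusting for it instead is a gain in precision, not a repair of bias.
- A reader might infer that 17% to 20% is this trial's error rate for every one of the 22 listed outcomes. It is conditional on village being ignored and on an ICC of 0.05. Service uptake and help seeking (outcome 10) is reported only as frequencies and percentages. The community outcomes have 18 respondents per village and no stated ICC.
- A reader might infer that the error must favour false claims. For a pooled two-wave regression that ignores both village and person, the test can be conservative.
- A reader might count the baseline balance tests ("Chi-square, ANOVA and t-tests will be performed to check whether the study arms are covariate balanced") as part of the fault. They do not enter the effect estimate, so nothing here turns on them.

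**Conclusion.** The point stands as a mismatch within the protocol. The design allows for village; the stated impact analysis does not. For outcomes among the girls, the consequence is a type I error of about 17% to 20% instead of 5% if clustering is ignored and the analysed outcome has the planned ICC, and about 7% to 14% at an ICC of 0.01 to 0.03. The planned value was set for a proportion, whereas the primary outcome is to be summed into a score, so 0.05 is an assumption for that outcome too. For change scores the size cannot be fixed from the protocol; the wide range above is itself a reason to name the model.

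This should be settled before the endline data are analysed, because it decides whether the primary p-value and confidence interval are valid. The baseline question is secondary: both contrasts are valid under randomisation, and the covariate form is never less precise under equal variances, apart from the small cost of estimating its slope. The design itself needs no change.

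**What to change.** Amend the impact paragraph under *Quantitative data analyses* in two respects.

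1. State that every inferential comparison of arms accounts for village, and name the method. Suitable choices are a mixed model with a village random effect, GEE or modified Poisson regression with village-clustered standard errors where risk ratios are wanted, or an analysis of village summaries. Whichever is chosen, specify a small-sample correction for 32 clusters.
2. For the girls and the husbands, replace the change-versus-change contrast by the endline outcome compared between arms with its own baseline value as covariate.

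The cost is protocol wording. No further villages, participants or measurements are needed, and the planned software can fit these models. Compared with an analysis that ignores village, confidence intervals for outcomes with positive ICC will usually be wider, which is the price of their being valid.
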